### Cost-effectiveness analysis (CEA)

In the CEA, the ratio of the difference in mean cost between the ELEVATE and Waitlist-control groups to the difference in effectiveness scores (change in GMFM-66) between groups will be used to estimate an incremental cost-effectiveness ratio (ICER) from the publicly funded healthcare payer and societal perspectives. The mean effectiveness for each group will be compared using patient level regression. We will use Ordinary least squares (OLS) to assess the difference in effectiveness and the difference in cost between groups. We will control for a set of covariates including study site, age and baseline GMFM-66 scores. The mean cost per participant for each group will also be compared using participant-level regression. A bootstrapped analysis will be conducted for the CEA and results presented on a cost-effectiveness acceptable curve (CEAC).

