### Randomization and stratification

Participants will undergo baseline assessments before randomization (Fig. 1). The randomization sequence was generated in Edmonton by a statistician. We used a permuted block design with a block size of 2–4. Randomization was stratified by city to ensure that the numbers allocated to the intervention and control groups will be roughly equal at each site. Their assignment is concealed until baseline assessments are complete, and are made available to the study sites through Research Electronic Data Capture (REDCap).

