#### Resource use and costing

Costs related to lower extremity therapy as well as resources used for treatment and management of the child’s cerebral palsy will be included over the study period, similar to a previously reported protocol [27]. The child will be the unit of analysis and utilization incurred by the participant, caregivers and/or the healthcare system will be assigned to the child for analysis. The Resource Use Questionnaire (RUQ) is a tool validated for use in participants with neurodevelopmental disabilities [28, 29] and will be used to collect information regarding resource use and out-of-pocket costs (e.g. physical or occupational therapy, materials and equipment, child-focussed recreation activities, etc.).

The RUQ will be administered at baseline, six months, the end of the one year study period and at the four-year-old follow up. The total cost per participant per month will be calculated and used in extrapolation. For the healthcare system perspective, costs will include physical or occupational therapy, child-focused recreation activities and additional services related to the child’s care paid for by the public healthcare system. For the societal perspective, costs will include all costs for the healthcare system perspective as well as parent lost productivity and parent out-of-pocket costs. For analysis using the societal perspective, a human capital approach [30] will be used to monetize lost caregiver productivity. Parent reports on the RUQ will include out-of-pocket costs for additional services, child-focused recreation activities, and materials and equipment. Lost productivity and out-of-pocket costs will be summed for the family of each participant to obtain total lost productivity and out of pocket costs for each participant over the study period.

The cost of the ELEVATE intervention will be estimated from the compensation to therapists including training, administration of the ELEVATE intervention and the cost of any materials and supplies associated with the intervention.

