### Sample size

The effect size on the primary outcome measure is estimated at 0.91, based on data from a cohort of children trained by their parents in our preliminary efficacy trial, as this is the more conservative estimate compared to the 1.67 effect size of children trained by a physical therapist. Twenty children per group are required to achieve statistical power of 0.8 and significance of 0.05. To account for cluster randomization with an estimated intra-cluster correlation coefficient of 0.02, a design effect of 1.4 is considered, which results in a total sample size of 56.

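### The covariates named for the cost regression leave out baseline resource-use cost, which is collected before randomisation; naming it would give a modest gain in precision

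*Protocol article*

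**What the plan says.** Under Cost-effectiveness analysis (CEA), the protocol article states: "We will use Ordinary least squares (OLS) to assess the difference in effectiveness and the difference in cost between groups". The next sentence gives the adjustment: "We will control for a set of covariates including study site, age and baseline GMFM-66 scores". It then adds "The mean cost per participant for each group will also be compared using participant-level regression". No separate covariate set is given for cost.

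Under Resource use and costing, the schedule is: "The RUQ will be administered at baseline, six months, the end of the one year study period and at the four-year-old follow up". Costs "will be included over the study period, similar to a previously reported protocol". The section does not say how the baseline questionnaire enters the analysis.

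Under Randomization and stratification, baseline assessments are placed before allocation, and city is the only stratification factor: "Randomization was stratified by city to ensure that the numbers allocated to the intervention and control groups will be roughly equal at each site".

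**The concern.** The incremental cost-effectiveness ratio has two components, and the named covariates treat them differently. The effect difference is adjusted for its own baseline (GMFM-66). The cost difference is adjusted for baseline motor score but, as far as the named list goes, not for baseline cost, although that measurement is planned before allocation.

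A family's earlier use of therapy, equipment and recreation services may well predict its later use. Stratification by city does not balance it within sites. If it is prognostic and left out, part of any chance difference between arms in prior spending stays in the incremental cost. Over repeated trials this appears as a larger standard error, a wider bootstrap cloud and a flatter acceptability curve. These are one loss of precision seen from several sides and should not be counted as separate harms.

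**Working it through.** **Inputs from the protocol article (Sample size).** "The effect size on the primary outcome measure is estimated at 0.91"; power 0.8; significance 0.05 (taken as two-sided); 20 per group; design effect 1.4; total 56.

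**Inputs not in the article, so assumed.** Equal allocation with all 56 children analysed, giving 56 / 2 = 28 per arm. The correlation r between baseline and follow-up cost is set at 0.3, 0.5 and 0.7. No cost SD is given, so results are in SD units.

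**1. The article's own figure.** A two-sample t-test with effect size 0.91, two-sided 0.05 and power 0.8 needs 19.96, that is 20 per arm. Then 40 × 1.4 = 56. The stated figure reproduces. It serves here only to supply the number per arm.

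**2. Chance imbalance in baseline cost.** SE of the difference in means = √(2/28) = 0.267 SD. Probability that it exceeds 0.25 SD in either direction: 0.25 / 0.267 = 0.94, so about 35% (normal approximation). Beyond 0.5 SD: about 6%.

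**3. What carries into the incremental cost.** Without adjustment the expected shift is r × imbalance.

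**4. Effect of adjustment.** SE after adjustment = 0.267 × √(1 − r²). Equivalent total sample size without adjustment = 56 / (1 − r²).

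| Assumed r | Shift from a 0.25 SD imbalance | Shift from a one-SE imbalance | √(1 − r²) | SE after adjustment | Cut in SE | Equivalent N |
|---|---|---|---|---|---|---|
| 0.3 | 0.075 SD | 0.08 SD | 0.954 | 0.255 SD | about 5% | 62 |
| 0.5 | 0.125 SD | 0.13 SD | 0.866 | 0.231 SD | about 13% | 75 |
| 0.7 | 0.175 SD | 0.19 SD | 0.714 | 0.191 SD | about 29% | 110 |

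**5. Check by simulation.** Least squares with 28 per arm and 20,000 replicates at each r, with normally distributed costs. Mean error was about zero with and without the covariate. The SE was about 0.27 unadjusted and 0.26, 0.235 and 0.192 adjusted. The adjusted values lie slightly above the formula, which ignores the cost of estimating one more coefficient.

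**6. Why these are upper bounds.** The table treats site, age and baseline GMFM-66 as explaining none of baseline cost. If they explain part of it, the model already captures some of the gain and adding baseline cost brings less.

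**The case against.** The strongest reply is that the covariate list is open. The word *including* means that site, age and baseline GMFM-66 need not be the whole set, and a fuller analysis plan, not shown, may name baseline cost. A condensed article may properly leave a full list to that plan. This stands as far as it goes: a reader might infer that the cost model controls for these three variables alone, and the text does not say so. What remains is that the article does choose to state covariates for the cost model, names the baseline of one outcome and not of the other, and gives the baseline RUQ no use. Naming it in advance also removes a choice that could otherwise be made after the cost data are seen.

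A reader might also infer that the incremental cost is biased. It is not. Allocation is random, the unadjusted difference has the right expectation, and the bootstrap already expresses chance imbalance as sampling variation.

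Nor does a baseline imbalance pass in full into the result. Only r times the imbalance does, so the 35% in step 2 is the chance of a baseline difference of that size, not of an equal shift in incremental cost.

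Finally, r is unsupported by the article. Children enter between eight months and three years of age, so past spending in the youngest may say little about later spending. The cost of ELEVATE itself follows allocation, and earlier spending need not predict it. These points stand and argue for weight on the lower end of the range.

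**Conclusion.** The point holds as a minor gain in precision for a secondary analysis. The covariates named for the cost regression omit a baseline cost measure that is planned before randomisation, and the article gives that measure no role. The incremental cost remains unbiased but is estimated less precisely than the planned data allow. The possible cut in its standard error runs from about 5% to about 29%, depending wholly on the assumed r, and these are ceilings. The primary GMFM-66 comparison is untouched. The conclusion rests on about 28 analysed children per arm, a baseline RUQ completed for them, and some persistence of spending within families, which is plausible but not shown in the article.

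**What to change.** In Cost-effectiveness analysis (CEA), add baseline RUQ monthly cost to the named covariates of the cost regression. Use the payer-perspective baseline in the payer analysis and the societal-perspective baseline in the societal analysis. Refit the same adjusted model in each bootstrap replicate, so that the ratio and the acceptability curve carry the gain. State in Resource use and costing that the baseline questionnaire serves only as this covariate and does not count towards the study-period cost total.

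The cost is one degree of freedom and a few words in the plan. No new data are needed. If r proves small, little is gained, but little is lost.

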### Trial monitoring

The trial is overseen by Health Canada because the PSAD is approved for investigational testing. The trial is monitored by the Quality Management in Clinical Research unit at the University of Alberta. The Research Ethics Board 3, University of Alberta, approved this study and the researchers are responsible for reporting protocol amendments and adverse events. Annual ethics renewals of the protocol are monitored by this Board.

## Qualitative study

### Design

Interpretative Description methodology [36] will be used as the methodological framework for the concurrent qualitative study to gain insight into the perspective of parents participating in a partnership with community therapists to administer the ELEVATE intervention. Interpretative Description has been chosen because this study intends to generate clinically relevant knowledge that is rich in description and interpretation and can be applied to improve clinical practice.

### Sample selection

Participants will be recruited from the multi-centre RCT and sampling will be purposive, to reflect the expected variation in experiences of participants [37]. We aim to interview parents with diverse backgrounds and experiences including individuals with varied socioeconomic status, multiple and single child families and single parent families. Sampling decisions will be made iteratively as information about participants’ experiences is explored and areas where further information is required becomes evident. Hence, a definitive sample size is not defined a priori but will be evaluated on an ongoing basis as data sufficiency becomes apparent or adequate to provide deep insight into the research question [38, 39]. We estimate an approximate sample size of 12–15 for the study, based on previous qualitative studies of parent experiences with home-based rehabilitation for children with CP [18].

### Data collection

Data will be collected through individual, semi-structured interviews at the start of intervention in the RCT and immediately following the intervention. Parents who choose not to participate in the RCT will be offered the opportunity to participate in a single interview to explore the barriers to participating in intensive rehabilitation. The interviews will follow a semi-structured interview guide (Supplementary File 1) at each time point. All interviews will be de-identified, audio recorded and transcribed verbatim.

### Data management and analysis

Thematic analysis will be used to organize and describe the data in rich detail. An inductive approach to thematic analysis will be used; themes will be strongly linked to the data [40], while interpreting findings with the intent to apply them to the practice of physical therapy. Data analysis will run concurrently with data collection to ensure that sampling and data collection are informed by emergent results. The coding process will involve interpretative thinking rather than simply recording and analyzing [41]. Field notes from interviews, including observations and interviewer impressions, will not be included in coding but will assist with interpreting transcripts.

### Rigour and credibility

The quality of this study will be enhanced by keeping a detailed record of activities, regular team meetings and ongoing reflexivity around the information being collected and the team members’ roles as clinician-researchers [42]. Detailed documentation will involve journaling and field notes following interviews. Modifications to the semi-structured interview guide will be documented as the team of researchers come to a deeper understanding of parents’ experiences throughout this study. Data analysis will be conducted collaboratively with at least two members of the research team.

## Discussion

Perinatal stroke results in life-long consequences for children and families. By intervening early, limited health care resources can be directed to children at an age when the effects are potentially largest. This study engages parents as partners so they become familiar with the principles of the approach. We anticipate that parent involvement will facilitate longer-term outcomes that will potentially enhance child motor development beyond the study period. We hypothesize that early improvements in gross motor function will enhance child outcomes and improve child and family quality of life. In addition, economic benefits may extend beyond our study period, for example, by delaying or avoiding the need for orthoses and botulinum toxin A injections, which we aim to capture at the four-year-old follow-up. Understanding parents’ experiences with the parent-therapist partnership model will allow for refinement of this approach to rehabilitation and more effective translation to clinical settings. Finally, partnering with key knowledge users, including families and pediatric clinicians, aims to bring about faster and more seamless adoption of the intervention if the results demonstrate effectiveness.

## Data Availability

Not applicable. Results from this trial will be uploaded to clinicaltrials.gov upon completion.

## Abbreviations

ELEVATE: Engaging the Lower Extremity Via Active Therapy Early
CP: Cerebral Palsy
RCT: Randomized Controlled Trial
REDCap: Research Electronic Data Capture
GMFM-66: Gross Motor Function Measure-66
PedsQL CP: Pediatric Quality of Life Inventory™ module for cerebral palsy
YC-PEM: Young Children's Participation and Environment Measure
PSAD: Portable Spasticity Assessment Device
